### Data collection and management

2.8

The whole process of data collection and recording is carried out by one or two assistants. Personal information about potential participants and registered participants will be collected, shared and stored in a separate storeroom to protect pro-trial, in-trial and post-trial confidentiality. The access to the database will be restricted to the researchers in this study team.

### Statistical analysis

2.9

The collected data are analyzed by SPSS 18.0 software. Chi-square test is used for counting data, mean ± standard deviation $\left(\bar{x}\pm \text{S}\right)$ is used for measurement data, independent sample *t* test is used for normal distribution, Mann–Whitney *U* test is used for skewed distribution, and the difference is considered to be statistically significant when *P* *<* .05.

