### Sample size

2.3

The calculation of sample size is based on treatment, the mean value and standard deviation of TCM syndrome score. According to the results of the pilot study, the experimental group is 13.32 ± 4.30, and that of the control group is 15.83 ± 3.82. Set α = 0.025, one-sided test, β = 0.20. Calculated by PASS15.0 software, each group needs 43 participants, the estimated withdrawal rate is 20%, and each group will include 54 participants.

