### Evaluation criteria and judgment of curative effect

2.7

1.TCM syndrome score: refer to the guiding principles of Clinical Research of New Drugs of Traditional Chinese Medicine (trial).^[18]^ The main symptoms and signs (including joint pain, joint swelling, limitation of joint activity, waist and knee soreness, fear of cold and cold, morning stiffness) are evaluated, and the scores are 0, 2, 4 and 6 respectively according to the severity, and the cumulative total score is the total score. The higher the total score, the more serious the illness.2.The Health Assessment Questionnaire Disability Index (HAQDI).^[19]^ According to the difficulty of completing 8 life-related actions (including dressing and grooming, getting up, eating, walking, personal hygiene, touching, grasping, activities, etc.), they are divided into 4 grades, corresponding to 0, 1, 2 and 3 points respectively. The HAQDI value is calculated by accumulating the 8 scores and calculating the average value. The higher the score is, the worse the quality of life is.

1.DAS-28 score ^[17]^:a)①DAS-28 score > 5.1 indicates high disease activity;b)②3.2 < DAS-28 score ≤ 5.1 indicates moderate disease activity;c)③2.6 < DAS-28 score ≤ 3.2 indicates low disease activity;d)④DAS-28 score ≤ 2.6 indicates basic remission of the disease.2.Laboratory examination: including serum calcium ion (Ca^2+^), ESR, hs-CRP, RF level.3.Adverse reactions: discomfort related to treatment occurred during treatment.

The above observation indexes are collected on the day before and after treatment. All patients are followed up for 2 months, and the data are collected according to the same standard in the first and second month.

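### Section 2.9 makes no use of the baseline scores and lets the observed distribution choose the test; prespecifying ANCOVA for the TCM score would gain precision at no cost

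*Protocol article*

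**What the plan says.** Section 2.9 of the protocol article gives two between-group methods for measurement data: "independent sample *t* test is used for normal distribution" and "Mann–Whitney *U* test is used for skewed distribution". It does not say how normality or skewness is judged, names no covariate, and does not say whether the test is applied to post-treatment values or to changes from baseline.

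Section 2.7 shows that baseline values will exist: "The above observation indexes are collected on the day before and after treatment". Two later visits follow: "All patients are followed up for 2 months, and the data are collected according to the same standard in the first and second month". For each item of the TCM syndrome score, "the scores are 0, 2, 4 and 6 respectively according to the severity".

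Section 2.3 sizes the trial on "the mean value and standard deviation of TCM syndrome score", with pilot values "the experimental group is 13.32 ± 4.30, and that of the control group is 15.83 ± 3.82" and error rates "Set α = 0.025, one-sided test, β = 0.20". No outcome is labelled primary, so the TCM score is called the sizing endpoint here. The second Study design section (2.5) describes 1:1 allocation and mentions no stratification by baseline severity.

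**The concern.** There are two separate issues.

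**Baseline is not used.** Each score is measured before treatment, and the stated tests take no covariate. If the baseline TCM score predicts the post-treatment score, adjusting for it removes part of the residual variance. It also removes the part of any chance baseline difference between arms that would otherwise carry into the estimate. Without adjustment, the trial pays for baseline data and gets no precision from them.

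**The data choose the test.** A t test compares means; a Mann–Whitney test compares rank orderings. Section 2.3 plans for a difference in means. If the observed distribution decides which test is run, the quantity compared for the sizing endpoint is not settled until the data have been seen, and no criterion is given for the decision.

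**Working it through.** **Inputs from section 2.3.** Means 13.32 and 15.83, SDs 4.30 and 3.82, one-sided alpha 0.025, power 80%, 43 evaluable and 54 enrolled per group.

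**Step 1: reproduce the plan's figure.**
- Difference: 15.83 − 13.32 = 2.51.
- Pooled SD: √((4.30² + 3.82²)/2) = 4.067. Standardised effect: 2.51/4.067 = 0.617.
- Noncentral-t power is 79.8% at 42 per group and 80.8% at 43, so 43 is needed. Then 43/(1 − 0.20) = 53.75, which rounds up to 54.

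The stated 43 and 54 reproduce. The sample size is right for the unadjusted comparison of means that it assumes.

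**Step 2: ANCOVA on the baseline score.** Residual SD = 4.067 × √(1 − ρ²), where ρ is the baseline–outcome correlation. The documents give no ρ, so a range is assumed.

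**Step 3: change scores, in case these were intended.** With equal variances at both times (assumed), SD = 4.067 × √(2(1 − ρ)).

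| Assumed ρ | Variance removed by ANCOVA (ρ²) | Power at 43: unadjusted post-treatment | Power at 43: change score | Power at 43: ANCOVA | Evaluable per group for 80% with ANCOVA | 95% CI half-width with ANCOVA |
|---|---|---|---|---|---|---|
| 0.3 | 9% | 81% | 67% | 84% | 39 | 1.66 |
| 0.5 | 25% | 81% | 81% | 90% | 32 | 1.51 |
| 0.7 | 49% | 81% | 95% | 98% | 23 | 1.25 |

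The unadjusted comparison needs 43 per group and has a CI half-width of 1.74 points. ANCOVA does better than both alternatives at each correlation.

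**Step 4: chance imbalance.** Assume that the baseline SD equals the outcome SD of 4.067 (the article gives no baseline SD). The standard error of the baseline difference between arms is then 4.067 × √(2/43) = 0.88 points. With equal SDs, a baseline difference of that size shifts the unadjusted outcome difference by ρ × 0.88. At ρ = 0.5 this is 0.44 points, and 0.44/2.51 = 17% of the planned effect.

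**Step 5: test selection by the data.** These results come from simulations at 43 per arm.
- *Type I error.* A mechanical Shapiro–Wilk rule that chose between the two tests gave 4.4% to 4.9% across normal, skewed and even-valued scores (6,000 replicates each). Taking the smaller of the two p values, which an unstated criterion does not rule out, gave 5.4% to 6.7%.
- *Power at the planned difference, even-valued scores (4,000 replicates).* About 81% with the t test, 79% with Mann–Whitney and 80% with Shapiro–Wilk selection.
- *How often the test would switch.* For normal scores rounded to even values, Shapiro–Wilk rejected in at least one arm in about half of trials (50% to 53% across runs). A skewness test did so in about 10%.

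**The case against.** The strongest reply is that nothing here is invalid. Over randomisation the unadjusted comparison is unbiased, and the trial was sized for exactly that comparison and delivers the 80% it promises. This stands. The loss is extra power not taken up, not a shortfall, and the imbalance in step 4 is a bias only conditional on the baseline difference that happens to occur.

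A second reply is that section 2.9 does not exclude change scores, which do use baseline. This also stands as a reading of the text, although the values in section 2.3 look like post-treatment scores. It does not rescue the plan: at ρ = 0.3 change scores do worse than ignoring baseline, at 0.5 they only match it, and they stay below ANCOVA throughout. At 0.7, however, the gap to ANCOVA is only 95% against 98%.

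A third reply is that a condensed article may leave covariates to an analysis plan that is not shown. That carries some weight, but the article is not silent: it names the tests and the rule for choosing between them.

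A reader might go further and infer that, because the TCM total takes only even values, the test will switch in about half of trials and so damage the result. The documents do not support this. Section 2.9 switches on skewness and names no Shapiro–Wilk or other normality test. The rejections come from granularity, not skewness, and a skewness test rejects far less often. When switching does occur, power and type I error barely move.

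A reader might also infer from the DAS-28 entry threshold that baseline severity varies widely and predicts the TCM outcome. DAS-28 is a different scale, and the article reports no baseline TCM mean, SD or correlation.

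**Conclusion.** The point holds as a worthwhile improvement in efficiency and clarity, not as an error of validity. Unadjusted power is 81% at 43 per group; ANCOVA raises it to between 84% and 98% for assumed correlations of 0.3 to 0.7. The gain is modest at the low end and large at the high end, and the article does not show where in the range this trial lies. The 0.44-point shift rests on two further assumptions: equal baseline and outcome SDs, and a correlation of 0.5.

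On test selection, what remains is that the choice between means and ranks for the sizing endpoint is left to the data without a stated criterion. This should be settled in advance for clarity of the estimand, not because error rates are at serious risk.

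**What to change.** State in section 2.9 that the post-treatment TCM syndrome score, as the endpoint that sized the trial, is analysed by ANCOVA with treatment group and baseline TCM score as terms. The result is the adjusted mean difference with its 95% CI, reported whatever the observed distribution, with the Mann–Whitney test as a sensitivity analysis only. Use the same model, each with its own baseline, for HAQDI and DAS-28.

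The cost is one or two sentences. No new data or extra patients are needed, ANCOVA is a standard procedure in the SPSS package already named, and the planned 43 evaluable and 54 enrolled per group can stay as they are.

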**Methods::**

This is a prospective randomized controlled trial to study the efficacy and safety of silver needles in the treatment of rheumatoid arthritis. Approved by the Clinical Research Ethics Committee of our hospital. The patients are randomly divided into a treatment group (silver needle treatment group) or control group (routine western medicine treatment group). The patients are followed up for 2 months after 4 weeks of treatment. Observation indicators include: TCM symptom score, HAQDI score, DAS-28 score, laboratory indicators, adverse reactions and so on. Data will be analyzed using the statistical software package SPSS version 18.0 (Chicago, IL).

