### Study design

2.5

Eligible participants are randomly assigned to either the treatment group or the control group in a 1:1 ratio using a central-network-based randomization tool. Random sequences are generated by SAS 9.3 software (SAS Institute, Cary, NC, USA) by independent statisticians who do not participate in the implementation of the experiment or statistical analysis. The clinical research coordinator enters participants’ information on the tablet and is given a random number. The research assistant gets the allocation of participants from the computer. Throughout the study, the research assistant is responsible for screening, recruiting participants, and assigning random numbers to participants who had been included. Given the operational nature of the intervention, participants and operators may be aware of random allocation. However, the evaluators of research results and the statisticians of data statistics and analysis do not know about the distribution.

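### The trial is sized on one TCM syndrome score comparison, but no outcome or visit is named as primary and one P < .05 rule covers them all

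*Protocol article*

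**What the plan says.** - **Sizing (protocol article, 2.3).** "The calculation of sample size is based on treatment, the mean value and standard deviation of TCM syndrome score". The error rates are given as "Set α = 0.025, one-sided test, β = 0.20", and the result is that "each group needs 43 participants, the estimated withdrawal rate is 20%, and each group will include 54 participants". The score is not called primary. The sentence mentions treatment, which may mean a post-treatment value, but it does not identify a visit.
- **Outcomes (Abstract, Methods; 2.7).** The abstract's list is unranked and open-ended: "Observation indicators include: TCM symptom score, HAQDI score, DAS-28 score, laboratory indicators, adverse reactions and so on". Section 2.7 describes the TCM score, HAQ-DI, DAS-28, four laboratory measures (serum calcium, ESR, hs-CRP, RF) and adverse reactions, with no order of importance.
- **Visits (2.7).** Data are taken before and after treatment, and then: "All patients are followed up for 2 months, and the data are collected according to the same standard in the first and second month". That makes three post-baseline assessments.
- **Decision rule (2.9).** Tests are assigned by data type, and "the difference is considered to be statistically significant when *P* *<* .05". No outcome or visit is treated differently from another.

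**The concern.** The sample size rests on the error rate of one test. The decision rule applies the same threshold to every difference and does not say which one answers the trial's question. Followed as written, the plan would let efficacy be concluded from whichever outcome or visit crosses the threshold, and the 2.5% behind the 43 per group would not describe that conclusion. The visits are also not interchangeable: the end-of-treatment assessment measures the effect of the course just given, while months 1 and 2 measure whether it persists after the stated 4 weeks. Because participants and operators may know the allocation (2.5), it matters more that the choice is fixed in advance.

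**Working it through.** **1. Reproduce the stated sample size.** Inputs from 2.3 and 2.5: "the experimental group is 13.32 ± 4.30, and that of the control group is 15.83 ± 3.82"; one-sided alpha 0.025; power 80%; allocation 1:1.
- Difference = 15.83 - 13.32 = 2.51.
- Pooled SD = sqrt((4.30² + 3.82²)/2) = 4.067.
- The normal approximation gives 42 per group. The noncentral t calculation gives power 0.798 at 42 and 0.808 at 43, hence 43.
- Withdrawal: 43/(1 - 0.20) = 53.75, rounded up to 54.

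The plan's 43 and 54 are confirmed. Two-sided 0.05 gives the same power at each n, so 2.3 and 2.9 agree if the P < .05 in 2.9 is two-sided.

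**2. Count the comparisons the text permits.** TCM score, HAQ-DI, DAS-28 and four laboratory measures make 7 numeric outcomes. With 3 post-baseline assessments, 7 × 3 = 21. Adverse reactions are left out and would add more.

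**3. False-positive chance if any of the 21 could carry the claim, with no true effect.** Under independence:
- either direction: 1 - 0.95^21 = 65.9%, against 5%;
- favouring silver needle: 1 - 0.975^21 = 41.2%, against 2.5%.

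The document gives no correlations, so a range is assumed: 0 to 0.7 between outcomes and 0 to 0.9 between visits. Simulating 21 correlated normal test statistics (200,000 draws per setting) gives:

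| Between outcomes | Between visits | Either direction (planned 5%) | Favouring silver needle (planned 2.5%) |
|---|---|---|---|
| 0 | 0 | 65.9% | 41.2% |
| 0 | 0.9 | 45.7% | 25.9% |
| 0.3 | 0.7 | 51.1% | 26.7% |
| 0.7 | 0 | 44.6% | 24.5% |
| 0.7 | 0.9 | 27.7% | 13.8% |

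In the favourable direction the multiple of the planned rate runs from 13.8/2.5 = 5.5 to 41.2/2.5 = 16.5.

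**4. The same chance if only the TCM score counts but its visit is open (3 tests).** Under independence it is 1 - 0.975³ = 7.3% favouring silver needle. With between-visit correlation 0.9 it is 4.2%. That is 1.7 to 2.9 times 2.5%. In either direction the range is 8.4% to 14.3%, against 5%.

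**5. Power under the alternatives, at 43 per group.**
- One named comparison at two-sided 0.05: about 81%.
- TCM score at three co-equal visits, Bonferroni 0.05/3: about 68%; about 55 evaluable per group needed for 80%.
- All 21 co-equal, Bonferroni 0.05/21: about 43%; about 80 evaluable per group needed.

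**The case against.** The best reply is that the document does single out an outcome. The sample size rests on the TCM syndrome score alone, and that score comes first in both the abstract and 2.7. Read this way, only the visit is open and the inflation is the modest one in step 4. This is a fair reading, and it is why that case must be reported beside the larger one. It does not remove the point: 2.3 does not call the score primary, 2.9 gives it no special status, and no visit is attached to it under any reading.

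A second reply is that 2.7 describes collection and 2.9 describes methods. Neither says that every outcome is tested at every visit, or that any one result below .05 would establish efficacy. That is correct. Twenty-one is the number the schedule and single rule allow, not a stated list of tests, and serum calcium and RF are unlikely routes to an efficacy claim.

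A third reply is that multiplicity procedures and the ordering of secondary outcomes are commonly left to an analysis plan, which is not shown. That also stands, and their absence is not criticised here. Naming the primary outcome and its time point is different: it defines the trial's question and belongs in the protocol.

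Measuring outcomes for two months after treatment is ordinary follow-up and is not a fault in itself.

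**Conclusion.** The point holds: the protocol fixes an error rate for one TCM syndrome score comparison, but leaves open whether that comparison decides the trial and when it is made. The size depends on the reading. If any of up to 21 comparisons could support efficacy, the chance of a false result favouring silver needle is 14-41% against 2.5%, with 41% requiring independence and the lower values resting on assumed correlations. If the TCM score is taken as the implied primary outcome, it is about 4-7%.

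A reader might infer that the false-positive rate is 66% against a planned 2.5%, or that it is always at least ten times too high. The documents do not support either. The 66% counts both directions and belongs beside 5%. The like-for-like multiple in the favourable direction is about 5.5 to 16.5 when all 21 count, and 1.7 to 2.9 when only the TCM score does. Nor is one-sided 0.025 in 2.3 in conflict with a two-sided .05 in 2.9. The stated sample size is not in question.

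**What to change.** State consistently in 2.3, 2.7 and 2.9 that the TCM syndrome score at one named visit (for example the end of the 4-week treatment) is the single primary comparison, tested at two-sided 0.05. Add that all other outcomes and visits are secondary or exploratory and cannot by themselves support the efficacy conclusion. An order for testing secondary outcomes is optional and can be left to the analysis plan.

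Make the change before any outcome data are examined by arm. Since participants and operators may know the allocation, unblinding is not a usable deadline.

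The cost is wording only, with no added patients or visits. The planned error rate is restored for the primary claim, and 43 evaluable per group keeps about 81% power under the pilot figures. The downside is that fewer results can be presented as confirmatory.

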## Discussion

3

At present, the pathogenesis of rheumatoid arthritis is not fully understood, which may be related to autoimmune factors, infection and heredity.^[20]^ No matter the duration of the disease, early and effective treatment of RA patients can reduce their disability rate, control the disease activity of patients, help to prevent and delay the disease of patients, and is also the key to the treatment of rheumatoid arthritis.^[21,22]^ Clinical observation found that non-steroidal anti-inflammatory drugs, anti-rheumatic drugs and steroid drugs and other drugs in the use process, in addition to toxic side effects, but also showed a gradual failure trend, and some patients will develop drug resistance, seriously reducing the therapeutic effect.^[23]^ Therefore, it is urgent to explore safe and effective complementary and alternative therapies.

Silver needle is a therapeutic method evolved from traditional acupuncture, which combines the advantages of acupuncture and moxibustion. Clinical studies have shown that acupuncture combined with needle handle heating can significantly improve local blood circulation, reduce muscle spasm, relieve pain,^[24]^ and reduce the levels of interleukin-6 (IL-6), interleukin-8 (IL-8) and tumor necrosis factor-α (TNF-α).^[25]^ Animal studies have found that silver needle treatment can increase the content of β-endorphin for analgesia,^[26]^ but also significantly reduce the content of interleukin-6, play the role of analgesia and anti-inflammation.^[27]^ Since there is no standard clinical study to evaluate the efficacy of silver needle in the treatment of rheumatoid arthritis, we intend to evaluate its efficacy and safety through prospective randomized controlled trials. This work is beneficial to both patients and decision makers in clinical practice.

This study is a single-center study, and the regionalization of the population may have a certain impact on the results. Therefore, more multicenter, large-sample randomized controlled trials are needed to verify our conclusions.
